### Sample size

Accepting a 0.05 Alpha risk and a beta risk of 0.2 in a bilateral contrast, it is required to have 67 patients in the control group and 67 in the intervention group (total: 134), to detect a difference equal to or greater than 600 steps/day (1/2 SD) between the 2 groups. It is assumed that the common standard deviation is 1200 steps and it has estimated losses of a 5% follow-up rate.

### Variables and measurement instruments

1. Principle Variable of the Study

It will be an evaluation of PA in the PWD and the CG, and there will be two measurements used:

1.1. The PA carried out during 7 days by the digital Pedometer (Omron Hj-321 lay-UPS) will be used to evaluate the primary endpoint of psychical activity, which had been previously validated [49]. Piezoelectric sensors use multiple-position sensing technology. The manufacturer of the pedometer describes that in this model, an acceleration waveform is generated from both sensors, and based on the size and shape of the waveforms, an algorithm selects the sensor that is used to count steps. The advantage of having two piezoelectric sensors in the pedometer is that it is not critical to position the pedometer perpendicular to the ground and upright at the hip to obtain accurate step counts. For example, if the pedometer is at an angle of 60- or more from the horizontal or at a slant, the pedometer can still accurately estimate steps. It features and displays total steps, aerobic steps, the distance traveled and calories consumed and it stores the results of the last 7 days. Calories burned: By measuring the intensity of your activity, the unit can calculate the amount of calories burned. Aerobic steps: Aerobic steps are counted separately when walking more than 60 steps per minute and more than 10 minutes continuously. If a rest of less than 1 minute is taken after a continuous walk of more than 10 minutes, this will be regarded as part of “a continuous walk”. The PWD and the CG will wear the pedometer, the subject will wear the pedometer on the right side of the waist on an elastic belt for 7 consecutive days. The initial evaluations will be at 6 months and 12 months.

1.2. They will complete a PA questionnaire: The PA is estimated by means of the 7-day Physical Activity Recall (7-PAR). The 7-PAR is a general measure of physical activity, which has been recognized as valid and reliable tool in recent years and is widely used in epidemiological, clinical and behavior change studies. It consists of a semi-structured interview (10-15 minutes) in which participants provide an estimate of the number of hours dedicated to physical or occupational activities requiring at least a moderate effort in the past seven days. The categories collected are moderate, vigorous, and very vigorous physical activity. The amount of time dedicated to each activity is multiplied by the mean metabolic equivalents (METs) of each category: light activity 1.5, moderate 4, vigorous 6, and very vigorous 10. The sum of the products of the hours dedicated to each activity and its estimated mean energy expenditure (MET) provides an estimation of the kilocalories per kilogram used per day (kcal*kg-1 * d-1). The dose of physical exercise will be estimated in METs/hour/week and active persons were considered as those doing at least 30 minutes of moderate activity, five days a week, or at least 20 minutes of vigorous activity, 3 days a week or 450 MET · min · wk^-1^. Persons not reaching this level of physical activity were considered sedentary [50].

2. Physical Activity Log:

2.1 They will be recorded the PA habits of the PWD and their relatives: places, schedules, habitual activities, leisure, instrumental, and sports activities; the adaptations to climatic and to seasonal; covered spaces, outdoor; at home or in institutions. The changes in the family care plan for increasing the PA. There are explanations on the possible discrepancies in registration of the pedometer and the 7-PAR questionnaire.

2.2 Contributions by medical staff and nurses on the implementation of program centers and on the degree of hospitality will be recorded to offer non-pharmacological therapy with the support of scientific evidence.

2.3 The evidence related to the PWD’s use of pedometers will be studied: mode of employment, possible loss, forgetfulness, improper use, etc.

3. Patients with Dementia:

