**Methods/Design:**

Design: Clinical, multicentric and randomized trial. A simple random sampling to select 134 patients diagnosed with dementia will be carried out. After contacting their relatives, his/her participation in the trial will be requested. A basal assessment will be made and the participants will be asigned to control or intervention group (1:1). Variables: The main measure will be the assessment of physical activity (podometer and 7-PAR) in patients and caregivers. In patients with dementia: ADAS-cog, functional degree and cardiovascular risk. In caregivers: cardiovascular risk, general health and quality of life. **Intervention**: For 3 months, participants will receive instructions to do physical activity with an adapted program. This program will be designed and applied by Primary Health Care professionals in patients with dementia and their caregivers. The control group will receive regular care. **Analysis:** An intention-to-treat analysis will be carried out by comparing the observed differences between basal, 6 and 12 months measures. Change in the mean of daily steps assessed with the podometer and 7-PAR will be the main result.

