### Hypothesis

There are studies that suggest that increasing PA in both PWD and CG seems to provide health benefits in both groups. However, there are no interventions that have demonstrated their effectiveness to ensure that both groups increase their PA.

Since the implementation of the project PEPAF in Primary Health Care it has been effective in increasing PA in inactive adults [8], especially among those over 50 years. We hope to demonstrate that a physical activity program that is adapted, designed, and applied by Primary Health Care professionals for patients with dementia and relative caregivers (predominantly women), is effective in increasing PA by 20% for PWD and their relative caregivers from Primary Health Care. Since the physical exercise seems to contribute and improve or slow down the cognitive impairment in PWD, we hope to reduce the ADAS-cog in PWD by 3 points. Since CVD and dementia are closely related—whether in the form of vascular cognitive impairment or in the form of Alzheimer’s Disease—and they share similar risk factors, if this program is effective, it may benefit people with dementia as well as relative caregivers, since it could help them maintain and improve their health, in particular the cognitive level of their patients and the cardiovascular problems of their CG which are derived from reduced physical activity due to the CG care tasks.

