### Statistical analysis

The analysis will take place using the intent- to-treat (ITT) The observed improvements will be compared between the basal measurement, at 6 and 12 months for each subject assigned to the intervention groups with respect to those assigned to the control group. The size of the effect will be defined as the change post-treatment in the experimental group less the change post-treatment in the control group, divided by the standard deviation combined. The effect of the intervention will be attributable to the differences in such improvements in these groups. A 95% confidence interval will be calculated. Predictor variables will be analyzed and confounding factors: sex, age, and it will be estimated the time’s effect on the repeated measurements that were carried out, using mixed linear regression models, fixed effects (time, intervention, interaction between time and intervention) and at random. The data was analyzed using IBM® SPSS® v.20 software.

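### The primary outcome is defined over two measures, two populations and two time points, but the sample size covers a single comparison of steps/day in patients

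*Protocol article*

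**What the plan says.** - **Measures and populations.** Under Variables and measurement instruments, item 1, the principal variable is introduced as follows: "It will be an evaluation of PA in the PWD and the CG, and there will be two measurements used". Items 1.1 (pedometer) and 1.2 (7-PAR) both sit under it. Item 1.1 ties the pedometer to the primary endpoint.
- **Main result.** The abstract (Methods/Design) says: "Change in the mean of daily steps assessed with the podometer and 7-PAR will be the main result".
- **Time.** Statistical analysis says: "The observed improvements will be compared between the basal measurement, at 6 and 12 months". It adds mixed linear models with time, intervention and their interaction. Neither 6 nor 12 months is named as primary. Objectives adds the aim of keeping the increase for at least one year.
- **Claim.** The Hypothesis section expects to show that the programme "is effective in increasing PA by 20% for PWD and their relative caregivers from Primary Health Care".
- **Size.** The Sample size section begins "Accepting a 0.05 Alpha risk and a beta risk of 0.2 in a bilateral contrast" and continues: "it is required to have 67 patients in the control group and 67 in the intervention group". The target is 600 steps/day with an SD of 1200 and 5% losses. No assumption is given for caregivers, for the 7-PAR or for a time point.

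**The concern.** A primary outcome needs one defined comparison, or a stated rule for combining several. Without that, neither the type I error nor the power of the main claim is defined. Here the outcome description allows up to 2 measures x 2 populations x 2 times = 8 comparisons, while the size calculation covers one.

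What is at stake depends on the success rule, which the article does not give. If a favourable result in any one comparison could carry the headline, the chance of a false claim exceeds 5%. If benefit must be shown in patients and in caregivers, as the hypothesis reads, the stated 80% is not the power of that claim. These two harms are alternatives; they do not add up.

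The choice of population is a real one. Methodological limitations says the authors cannot estimate whether patients or caregivers will respond more, so the headline population could be settled after the results are known.

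**Working it through.** **1. The plan's own figure.** Inputs from Sample size: alpha 0.05 two-sided, power 0.80, difference 600, SD 1200, losses 5%.

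n per arm = 2 x (1.960 + 0.842)² x (1200/600)² = 62.8, so 63 evaluable. 63/0.95 = 66.3, so 67 randomised per arm and 134 in total. The stated figure reproduces. With 63 evaluable per arm the normal-approximation power is 80.1%. This holds for one contrast, in one population, on one measure, at one time.

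**2. What the outcome text covers.** Taking pedometer steps alone leaves 2 populations x 2 times = 4 comparisons. Giving the 7-PAR the equal standing it has in the abstract makes 8.

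**3. If any one success at 5% sufficed.** With independent tests the chance of at least one false positive is 1 - 0.95^k:
- k = 4: 1 - 0.95^4 = 18.5%
- k = 8: 1 - 0.95^8 = 33.7%

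Independence is the extreme case. These are the same people at two times, pairs that share the programme, and two instruments for one construct. The article gives no correlations, so a common correlation was assumed and simulated:

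| Assumed correlation | 4 comparisons | 8 comparisons |
|---|---|---|
| 0 | 18.5% | 33.7% |
| 0.3 | 17% | 30% |
| 0.5 | 16% | 25% |
| 0.7 | 13% | 19% |
| 0.9 | 9% | 12% |

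**4. If both populations had to succeed**, on one measure at one time and each at 5%, there is no inflation across populations. The pair is the unit randomised (Baseline evaluation and follow-up), so caregiver numbers per arm would match patient numbers if each pair contributes one caregiver. Assuming 63 evaluable per arm and a 0.5 SD effect in caregivers as well, which the article does not state, each test statistic has expected value 0.5/√(2/63) = 2.81. The probability that both exceed 1.96 is:

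| Assumed correlation | Joint power |
|---|---|
| 0 | 64% (0.801 x 0.801) |
| 0.3 | 67% |
| 0.5 | 69% |
| 0.7 | 71% |
| 0.9 | 75% |

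**5. The measures, set side by side.** Item 1.1 and the steps/day sizing point to the pedometer as primary. The abstract joins the 7-PAR to it as the main result. Item 1.2 shows that the 7-PAR yields MET-weighted hours, so it is a second outcome on another scale and not another reading of daily steps.

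**The case against.** Several points on the other side are fair.

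- **Eight tests, each at 5%.** A reader might infer this and conclude that the false-positive rate is about one third. The article does not say so. It mentions 0.05 once, for one contrast, and the mixed model could cover both follow-up times in a single analysis. The 34% also needs independence and an any-one-wins rule, and neither is stated. What remains is that no contrast from the model is singled out.
- **No ordering at all.** This would be too strong. Item 1.1 and the size calculation lean towards the pedometer, and the one-year aim leans towards 12 months without making it primary. The populations are not ranked, and the abstract still conflicts with item 1.1 on the measures.
- **Alpha control may sit in a document not shown.** Agreed, and its absence here is not part of the point. Which comparison is primary and what the sample size covers are matters that this article does address, and it does so inconsistently.
- **Caregivers are enrolled too.** Because pairs are randomised, a caregiver comparison would have similar power if the same 0.5 SD effect applied. The gap is an unstated assumption, not an unsampled population.
- **The abstract sentence may just be awkward.** It can be read as steps by pedometer, plus the 7-PAR. Even so, it gives the 7-PAR equal standing.

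**Conclusion.** The point holds in a limited form: the primary outcome is defined as multiple and sized as single. The 67 per arm is correct for one steps/day contrast in patients, and nothing here shows it to be miscalculated.

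The stated 80% does not describe a claim of benefit in both populations. For that claim on one measure at one time, power would be about 64% to 75%, given an equal standardised effect in caregivers and correlations from 0 to 0.9. If instead any one comparison could support the claim at 5%, the error would be about 9% to 19% for the four pedometer comparisons and 12% to 34% for all eight, over the same assumed range. Only one of these consequences can apply, and the article does not settle which.

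The conflict over measures and the lack of a named time point and success rule stand whatever the correlations are.

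**What to change.** Before any outcome data are seen:

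1. Name pedometer steps/day as the primary measure and make the 7-PAR secondary. Correct the abstract and item 1 to match.
2. Name one primary time point, as a single between-arm contrast from the mixed model. Twelve months would match the one-year aim in Objectives.
3. State the success rule across populations. Either test patients first and then caregivers in fixed sequence, each at 5%, or require both, each at 5%.
4. Say in Sample size that the 80% applies to the patient steps/day contrast only. If both populations are required, state the caregiver effect and SD assumed and give the joint power.

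**Cost.** The changes are to wording, and 67 per arm stands for the patient contrast. Under the fixed sequence, a caregiver benefit cannot be claimed as confirmed if the patient test fails. That matters here because the authors do not know which group will respond more. Under the both-required rule, the reported power becomes less favourable. Restoring 80% joint power under independence would need √0.80 = 89.4% power per test: 83 evaluable per arm, and 83/0.95 = 87.4, so 88 randomised per arm instead of 67. That would be a change of size and not of wording. The sponsor may instead keep 67 per arm and report the lower joint power openly.

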### Baseline evaluation and follow-up

The initial information will be collected in the 1^st^ visit: It’s comprised of 3 groups of assessments (carried out by different professionals): A) The initial (health) screening: diagnostic criteria, GDS, dementia (Blessed, Timlison and Roth, 1968), informed consent, characteristics of care (duration, intensity, social support), informant questionnaire (TIN), socio-demographic data, comorbidity. B) Psychology: a) Patient: Mini Mental State Examination, ADAS-cog, 7-Minute Screen Test. C) Nursing: Cardiovascular evaluation, anthropometric measures, pedometers. b) The caregiver: Quality of Life (SF-12), Overload and burden (Zarit Breve), Mental Health (GHQ-12), Family Functioning (APGAR-F). In VISIT 2, after 7 days, the pedometers and activity log will be collected (7-PAR); It will be confirmed to the Principal Investigator that the initial information is complete and the pair will be assigned to the corresponding group (intervention or control (1:1) according to the previously maid random sequence. At 6 and 12 months the baseline evaluation will be repeated for both the CG and PWD. The flow chart (Figure 1) details the phases and steps in the development of the clinical trial.

Information on the activities carried out, difficulties in performing them, activity log, etc. will be collected during the interviews when the pedometer is collected. After the 6 month evaluation, there will be at least one meeting with the caregivers in the intervention group and another with the control group to complete the information about the development of the program and the proposals that have been considered more efficient to better record the PA (use of pedometers, etc.) and, in the intervention group, contributions are also prompted to increase the PA in their environment.

### Intervention

During the 3 months they will receive instructions to perform PA autonomously (walking, preferably in the vicinity of the place of residence). The intervention will be conducted by a professional from the health center so only pairs from the intervention group will have knowledge of the specific recommendations of the AFISDEMYF. There will be a 15-minute interview each month. This is an intervention that has demonstrated its effectiveness in the PEPAF study [8] and adapted, designed, and been implemented by Primary Health Care professionals for dementia patients and their relative caregivers.

### Assessing allocation concealment

The researcher who will make the randomization will be a different researcher to the one making the assessment. Nursing and psychology professionals whom are not informed about the group that each participant belongs shall make the evaluation visits. The subjects of both groups may participate freely in any other activity during the intervention period and will continue to participate in those that have been previously initiated.

### Timeline

In 2013 the ethics committee approved the study, and the evaluation questionnaires and procedure manuals were drafted. Recruiting of the pairs and baseline assessments will take place in 2014. Every pair will be evaluated again at 6 and 12 months, including the measurements from the initial phase. Starting from the third quarter in 2014, there will be meetings held with successive groups of 10–12 caregivers to complete the information on the difficulties encountered when increasing the PA for the PWD as well as the caregivers and on the difficulties that are observed in order to quantify the amount, intensity and duration of the PA that the PWD performs. In the last stage of the project, a physical activity program guide will be developed for patients with dementia and their relative caregivers, and a technical report on the characteristics and recommendations for designing pedometers that are adapted to the PWD with the aim of facilitating their commercialization and incorporate them into “memory stores”.

### Statistical analysis

The analysis will take place using the intent- to-treat (ITT) The observed improvements will be compared between the basal measurement, at 6 and 12 months for each subject assigned to the intervention groups with respect to those assigned to the control group. The size of the effect will be defined as the change post-treatment in the experimental group less the change post-treatment in the control group, divided by the standard deviation combined. The effect of the intervention will be attributable to the differences in such improvements in these groups. A 95% confidence interval will be calculated. Predictor variables will be analyzed and confounding factors: sex, age, and it will be estimated the time’s effect on the repeated measurements that were carried out, using mixed linear regression models, fixed effects (time, intervention, interaction between time and intervention) and at random. The data was analyzed using IBM® SPSS® v.20 software.

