
### Evaluation of the therapeutic interventions for dementia

There are many difficulties when assessing the effectiveness of the RCTs done on the PWD, both in general and for Alzheimer’s Disease. Therefore, both the Food and Drug Administration (FDA) and the European Medicines Agency (EMEA) have developed several guides to oversee RCTs in patients with AD. It should be noted that in RCTs on Alzheimer’s Disease drugs the Evaluation Scale of Behavior-Cognitive Section (ADAS-cog) has been used almost unanimously as a measure of cognitive performance [18,46]. It is a test that provides clinically significant information, which is well considered on a conceptual and neuropsychological basis [47]. The use of the ADAS-cog as a fundamental measure of the cognitive state should be permitted to draw comparisons with the results from other NPT or even with the RCTs, taking all this into account as it has been proposed in recent trials [15,18] and that is why this measure is proposed for our intervention. Due to the multidimensional nature of PA, there is no ideal way to measure PA since it occurs in natural contexts in a set of complex leisure and instrumental behaviors. These behaviors are conducted at different levels of intensity, duration, and with different frequencies, both within one day and in different seasons of the year. Also PA involves different parts of the body that make that the measure of PA is more effective in some circumstances than in others. The majority of research for evaluating PA has been mainly in adolescents. It is necessary to carry out research that can provide information about the difficulties of measuring PA in PWD. Self-report questionnaires are the most utilized methods for evaluating PA in research. The simultaneous involvement of the accompanying family member of the PWD during the walks, as well as the completion of a validated questionnaire (7-PAR), should provide important information on the possible relationship between the characteristics of PA and PWD. A very important drawback to evaluating PA in PWD based upon the tests carried out, is related to the large variability observed in terms of the dosage (intensity and duration), modality (aerobic, muscle endurance, etc.) and scope of preparation (at the home of the patient [13,48], in residences or in hospital). In order to quantify the exercise dosage, it is important to use objective instruments to measure in this project, such as digital pedometers. On one hand it is important to know PA habits of the PWD and relatives, and on the other hand the effects of increasing their PA.

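### Calendar season is not among the named model terms, although each 6-month visit falls half a year from baseline; this can cost precision at 6 months and blur the time effect, but does not bias the treatment comparison

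*Protocol article*

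**What the plan says.** - Under Statistical analysis, the effect is the change in the intervention arm minus the change in the control arm. The mixed linear model has fixed effects for time, intervention and their interaction, plus random effects. The text also says: "Predictor variables will be analyzed and confounding factors: sex, age". It states that the effect of time on the repeated measurements will itself be estimated.
- The background section on evaluating interventions for dementia says that activity occurs "with different frequencies, both within one day and in different seasons of the year".
- The physical activity log under Variables and measurement instruments is to capture "the adaptations to climatic and to seasonal".
- The Timeline says: "Recruiting of the pairs and baseline assessments will take place in 2014". Every pair is reassessed at 6 and 12 months. The distribution of entry over the year is not given.
- The Intervention section describes autonomous walking, preferably close to home.
- Under Sample size, 67 per arm are required "to detect a difference equal to or greater than 600 steps/day (1/2 SD) between the 2 groups". The same section adds: "It is assumed that the common standard deviation is 1200 steps".

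**The concern.** The article identifies season as a source of variation in its primary outcome, but the terms it names for the model leave season out. The visit schedule makes this matter more at one visit than the other. Six months after baseline the season is reversed; twelve months after, it is the same again.

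A common time effect removes only the average seasonal shift at a visit. A pair that enters in a low-activity season shifts upward by month 6, and a pair that enters in a high-activity season shifts downward. With entry spread over the year, these opposite shifts stay in the residual of the 6-month change and are absent from the 12-month change.

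Two things are at stake: the precision of the 6-month contrast, and the meaning of the time effect that the plan intends to estimate. Concurrent controls do not protect the latter.

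**Working it through.** **1. The plan's own figure.** Inputs from Sample size: "Accepting a 0.05 Alpha risk and a beta risk of 0.2 in a bilateral contrast", a difference of 600 steps/day, SD 1200, 5% losses.

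n per arm = 2 (1.960 + 0.842)² (1200/600)² = 2 × 7.85 × 4 = 62.8, so 63. Allowing for losses, 63/0.95 = 66.3, so 67 per arm and 134 in total. The stated figure reproduces. About 64 completers per arm are expected (67 × 0.95 = 63.7).

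**2. Seasonal shift in the change score.** Assume a yearly cosine of amplitude A steps/day (half of peak to trough) and let φ be a pair's point in the year at baseline.

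- 6-month change: A cos(φ + π) − A cos φ = −2A cos φ
- 12-month change: 0

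With entry even over the year, the 6-month shift has mean 0 and variance 4A² × ½ = 2A².

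**3. Size with year-round entry.** Take 1200 as the SD at each visit and r as the baseline to follow-up correlation (assumed 0.5 to 0.7). The change variance without season is 2 × 1200² × (1 − r): 1,440,000 at r = 0.5 and 864,000 at r = 0.7. The standard error of the between-arm difference is √(2 × variance/64).

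| A (assumed) | 2A² | Share of change variance, r = 0.5 | SE, r = 0.5 | Share, r = 0.7 | SE, r = 0.7 |
|---|---|---|---|---|---|
| 0 | 0 | 0 | 212 | 0 | 164 |
| 200 | 80,000 | 5.6% | 218 | 9.3% | 172 |
| 300 | 180,000 | 12.5% | 225 | 20.8% | 181 |
| 400 | 320,000 | 22.2% | 235 | 37.0% | 192 |

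At r = 0.5 the SD of change without season is again 1200. Power for 600 steps with 64 per arm is then 80.7% at A = 0, 76.0% at A = 300 and 68.3% at A = 500.

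**4. Size with clustered entry.** If all pairs enter in the quarter centred on the seasonal peak, the mean 6-month shift is −2A × sin(π/4)/(π/4) = −1.80A, or −540 steps/day at A = 300. Around the trough it is +540. This shift is common to both arms. The remaining seasonal variance is only about 0.03A², so the SE stays at about 212. With entry over one half-year, the seasonal variance is (2 − 16/π²)A², about 0.38A², and the SE is about 215 at A = 300 and r = 0.5.

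**5. Bias check by simulation.** With 4000 runs, 64 per arm, a true difference of 600, A = 300 or 500, and entry either year-round or in one quarter, the mean between-arm difference was 596 to 605 at 6 months and 595 to 603 at 12 months. With year-round entry, the spread of the 6-month estimate was 226 at A = 300 and 246 at A = 500, against about 210 without season. The 12-month spread did not change.

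**The case against.** The strongest reply is that the estimand is a between-arm difference in change under concurrent 1:1 randomisation of pairs. Season affects both arms alike and is not a confounder. This stands, and the simulation bears it out. A reader might infer that season inflates the 6-month effect, or might set a within-arm seasonal shift of several hundred steps beside the 600-step target. Neither inference is supported: the shift cancels between arms, can go in either direction, and is not the same kind of quantity as the 600-step difference.

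Other points also stand:

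- The variance cost and the mean shift need different entry patterns and do not occur together at full size.
- A reader might expect seasonal effect modification to imitate loss or maintenance of effect between 6 and 12 months. With even entry, each visit covers all seasons and such modification averages out equally. The spurious pattern needs both clustered entry and effect modification, and the documents establish neither.
- Sample size does not say whether 1200 is an SD of level or of change, or whether it already includes season. If it does, adding 2A² counts season twice.
- At r = 0.7, even A = 400 gives an SE of 192, below the 212 implied by the planning SD.
- The article also refers to unspecified predictor variables, so one cannot say that sex and age are the only adjustment. A fuller analysis plan may go further.

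These replies limit the size of the point without removing it. The article does state its model terms and named confounders, and season is not among them although the article recognises it. The planned estimate of the time effect has no protection from randomisation.

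**Conclusion.** The point holds as a low-cost improvement, not as an error that biases the treatment effect.

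With entry spread over 2014, leaving season out can raise the SE of the 6-month contrast by about 6% at r = 0.5 (225/212) or 10% at r = 0.7 (181/164), for an assumed amplitude of 300 steps/day. The 12-month contrast is unaffected. With clustered entry the precision cost is negligible, but the time term and any within-arm 6-month change cannot be read as the course of activity.

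The sizes rest on assumptions that the documents do not settle: a cosine pattern, its amplitude, the correlation between visits, the entry pattern, and a planning SD that excludes season.

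**What to change.** Add the calendar date of each pedometer week to the mixed model as a time-varying covariate, either as sine and cosine of day of year or as calendar quarter. State that the time term and within-arm 6-month changes will not be interpreted as the course of activity without this adjustment. Any season-by-intervention term should be labelled exploratory.

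The change is to analysis wording. It needs the date of each pedometer week, which visit records should supply, although the article does not say so. It costs two degrees of freedom for sine and cosine, or three for quarter. It can recover at most the precision loss shown above. If entry turns out to be clustered, season is nearly collinear with visit and little is gained; the report should then say that time and season cannot be separated.
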